**Diet intervention**

Subjects will be provided with energy-restricted diets of 1300-2200 kcal/day based on weight. The energy percentages provided by protein, fat and carbohydrate are 20%, 20% and 60% respectively, and energy distributions at breakfast, lunch and dinner are 30%, 40% and 30% respectively. All meals will be prepared and supervised by registered professional dietitians during the diet intervention.

**Exercise training**

Subjects will perform a training program 6 days/week for 8 weeks. The program is primarily comprised of endurance exercise such as bicycling, walking, running, dancing and ball games for 5 hours/day. It is also supplemented with resistance exercise. The endurance exercises involve moderate-intensity exercise training and high-intensity exercise training. The intensity of moderate-intensity training is set at 70-85% of the subject’s maximum heart rate (HRmax), which is calculated with the formula of 208 – (0.7×age). Heart rate will be continuously monitored by Polar heart rate monitors and recorded by researchers. The high-intensity exercise training (~90% of HRmax) is alternated with low-intensity exercise (~60% of HRmax) during the training. Resistance exercise is conducted with an intensity of 12-15 RM. The exercise program is designed to result in an energy expenditure of 1500-2500 kcal/day. Qualified trainers will supervise the subjects during the training program.

**Primary and secondary outcomes**

Primary outcome is endothelial function which is assessed by FMD. Secondary outcomes include anthropometry, resting heart rate, blood pressure, body composition, aerobic fitness, maximal strength, EPC number and function, arterial stiffness (cfPWV, baPWV, central blood pressure, and augmentation index (AIx)), cardiac autonomic function (standard deviation of normal-to-normal intervals (SDNN), square root of the mean squared differences of successive normal-to-normal intervals (RMSSD), total power (TF), low-frequency power in normalized units (LFnu), high-frequency power in normalized units (HFnu), and low-frequency power/high-frequency power (LF/HF)), and multiple biochemical markers (lipid profiles, insulin, tumor necrosis factor-alpha, high-sensitivity C-reactive protein, superoxide dismutase, vascular endothelial growth factor, endothelial nitric oxide synthase, adiponectin and irisin).

- 1. **Sample size**

Sample size is calculated based on 1% change in FMD after weight loss with an expected standard deviation in FMD from our laboratory of 1.3%. The sample size required for the study, with an α of 0.05 and β of 0.20 at 5% level of significance (two-sided) and estimating a refusal rate of 20%, is 20 subjects.

- 1. **Measurement procedures**

**Anthropometry and body composition**

Height and weight will be measured to calculate BMI (kg/m^2^). Body composition will be determined using a body composition analyzer (Inbody 370, Biospace, Seoul, Korea).

**Resting heart rate and brachial blood pressure**

Resting heart rate (HR) and brachial systolic / diastolic blood pressure (SBP / DBP) will be measured in triplicate using a sphygmomanometer while the subjects are seated for at least 10 min, and the average of the three readings will be recorded.

**Aerobic fitness**

Aerobic fitness will be assessed using the Physical Working Capacity test on a cycle ergometer (Ergoselect 100, Ergoline, Bitz, Germany) at a heart rate of 150 beats per minute (PWC150) or 170 beats per minute (PWC170). Heart rate will be measured with a Polar heart rate monitor. Prior to the test, subjects will be instructed to pedal with a steady cadence of 60 revolutions per minute. The start power is 50 watts (W) and is followed by a gradual rise of 25 W for PWC150 or 50 W for PWC170 every 2 min until the targeted heart rate (150 bpm or 170 bpm) is achieved and maintained at the steady state. PWC150 or PWC170 is calculated as the power relative to body mass (W/kg) corresponding to the heart rate of 150 bpm or 170 bpm, respectively.

**Maximum strength test (1RM)**

The maximum strength is determined by the one repetition maximum (1RM) bench press test. The 1RM test will be administered after each subject performed two warm-up sets. The warm-up sets are a pyramid system of increasing weight and decreasing repetitions. After all warm-up sets are completed, the subject will then attempt the 1RM.

**Endothelial function**

Endothelial function will be assessed by brachial artery FMD using echography (UNEX-EF, UNEX Co. Ltd., Nagoya, Japan). The subjects will rest in the supine position for 30 min in a quiet air-conditioned room, and then the right brachial artery will be scanned in longitudinal sections 2-10 cm above the elbow. A pneumatic cuff will be placed around the forearm and will be inflated for 5 min to at least 50 mmHg above systolic pressure. The brachial artery will be scanned and its baseline diameter will be recorded before cuff inflation, and then continuously from the release point to 2 min after cuff deflation to obtain the maximum diameter during reactive hyperemia. FMD is calculated as the maximum percent increase in arterial diameter during continuous measurement of arterial diameter following cuff deflation. Subsequently, endothelium-independent dilation will be measured by administrating 500 µg of nitroglycerine (NTG) sublingually.

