**Participants**

Obese adults from a traditional weight loss camp will be recruited to this study. The closed weight loss camp has uniformly managed accommodations, a controlled diet, and required physical training during the 8-week intervention period. The campers will be housed in the same building and could not move in and out freely during their stay. The measurements will be conducted before and after the subjects completed this 8-week weight loss program of exercise and diet.

Informed consent will be obtained from each individual prior to the measurements. This study will be conducted according to the Declaration of Helsinki. And the study will obtain approval from the Ethics Committee of Guangzhou Sport University.

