**EPC adhesion assay**

For the EPC adhesion assay, EPCs will be isolated and resuspended in M199 medium with 5% FBS. An equivalent amount of cells will be placed on a fibronectin-coated 96-well plate and incubated at 37˚C in 5% CO_2_ for 6 hours. After two gentle washes with PBS, adherent cells will be counted by independent, blinded investigators.

- 1. **Data analysis**

Analyses will be performed using SPSS 16.0 (SPSS 16, SPSS Inc., Chicago, IL, USA). Paired-sample t-tests will be used to compare the effects of an 8-week intervention of exercise and diet on different variables. Pearson’s correlation will be calculated to determine associations. The descriptive analyses will calculate the mean and standard deviations for continuous and percentages for categorical variables. A P-value < 0.05 will be used to indicate statistical significance.

•

•

•

•

1. **References**

Brook, R.D. (2006). Obesity, weight loss, and vascular function. *Endocrine* 29(1)**,** 21-25. doi: 10.1385/ENDO:29:1:121.

Collaboration, N.C.D.R.F. (2016). Trends in adult body-mass index in 200 countries from 1975 to 2014: a pooled analysis of 1698 population-based measurement studies with 19.2 million participants. *Lancet* 387(10026)**,** 1377-1396. doi: 10.1016/S0140-6736(16)30054-X.

Korkmaz, H., and Onalan, O. (2008). Evaluation of endothelial dysfunction: flow-mediated dilation. *Endothelium* 15(4)**,** 157-163. doi: 10.1080/10623320802228872.

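### No masked reading is specified for FMD, the primary outcome, although two secondary EPC assays have one; in a single-group before-after design a visit-related reading shift counts as effect

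*Protocol*

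**What the plan says.** Under Primary and secondary outcomes: "Primary outcome is endothelial function which is assessed by FMD". Under Participants, the timing is: "The measurements will be conducted before and after the subjects completed this 8-week weight loss program of exercise and diet". No control group is described, and Data analysis names a paired t-test.

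The Endothelial function section gives the device, rest period, scan region (a band 2 to 10 cm above the elbow), cuff procedure and formula. On the reading it says "The brachial artery will be scanned and its baseline diameter will be recorded before cuff inflation", followed by continuous scanning for 2 minutes after cuff release to find the maximum. It names no reader and does not mention masking.

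The laboratory sections differ among themselves. In the EPC adhesion assay, "adherent cells will be counted by independent, blinded investigators", and the EPC migration assay has the same safeguard for its manual count. The section on flow-cytometric EPC number has no masking statement.

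The sample size rests on FMD: "Sample size is calculated based on 1% change in FMD after weight loss", with an "expected standard deviation in FMD from our laboratory of 1.3" percent.

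**The concern.** The protocol treats reader expectation as a risk for two secondary assays and guards against it there. It writes no such guard for the outcome that carries the sample size and the main conclusion.

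The design makes this matter. Within each subject the pre-camp measurement always comes before the post-camp one, and there is no concurrent group in which a reading shift would also appear and be subtracted out. Suppose the reading runs slightly higher after the camp, through expectation or through change in practice. The mean paired difference then contains that shift in full. The paired t-test measures the difference against its random scatter and cannot tell a reading shift from a vascular change. No later analysis can remove it, so the protection has to be in the measurement procedure.

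**Working it through.** **Inputs.** From the Sample size section: planned change 1 FMD point, SD 1.3, two-sided α 0.05, β 0.20, 20% refusal, 20 subjects. From Data analysis: paired t-test. Arterial diameter is not given, so 3 to 5 mm is assumed.

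**1. Reproduce the planned sample size.** Take 1.3 as the SD of the within-subject change, so the standardised effect is 1/1.3 = 0.769. With the noncentral t distribution, power is 0.791 at n = 15 and 0.820 at n = 16, so 16 evaluable subjects are needed. Then 16/(1 − 0.20) = 20, which matches the protocol.

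**2. Effect of a reading shift b when the true change is zero.** The t statistic has noncentrality b·√n/SD. At n = 16 it is compared with the two-sided 5% critical value on 15 degrees of freedom, 2.131.

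| Shift b (FMD points) | Noncentrality, b × 4/1.3 | Chance of p < 0.05, n = 16 | Same, n = 20 |
|---|---|---|---|
| 0 | 0 | 5% | 5% |
| 0.25 | 0.769 | 11% | 13% |
| 0.5 | 1.538 | 30% | 37% |
| 1.0 | 3.077 | 82% | 90% |

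More subjects make this worse, because the shift does not average out.

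**3. Sensitivity to the SD.** The protocol does not say whether 1.3 is the SD of FMD or of its change. If it is the SD of FMD, the SD of the change is 1.3 × √(2(1 − r)), where r is the before-after correlation. At n = 16:

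| Assumed r | SD of change | b = 0.25 | b = 0.5 | b = 1.0 |
|---|---|---|---|---|
| 0 | 1.84 | 8% | 17.5% | 53% |
| 0.5 | 1.30 | 11% | 30% | 82% |
| 0.7 | 1.01 | 15% | 46% | 96% |

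The direction is the same throughout. The figures at SD 1.3 are the ones consistent with the plan's own N.

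**4. What one FMD point means in millimetres.** FMD = 100 × (maximum − baseline)/baseline. An error e in the maximum alone moves FMD by 100 × e/baseline, so one point corresponds to e = 0.01 × baseline: 0.03 mm at 3 mm, 0.04 mm at 4 mm, 0.05 mm at 5 mm. An error in the baseline diameter alone needs a similar size: 0.028 to 0.047 mm over the same range, for an assumed FMD of 5%.

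If both diameters at a visit are read 0.04 mm too large, FMD changes only from 5% to 100 × (1.05 × baseline + 0.04)/(baseline + 0.04) − 100. That is a change of −0.07 points at 3 mm, −0.05 at 4 mm and −0.04 at 5 mm. A common calibration drift therefore nearly cancels, and the concern is error that falls on one of the two diameters.

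**The case against.** The strongest reply is that silence is not an unmasked reading. The section names a dedicated FMD device and continuous diameter measurement, and it describes no manual frame selection. The two assays with masking are counts by eye (the migration section says they are made manually), where the need is more obvious. If the device derives diameters automatically, a reader may have little discretion. This stands in part. A reader might infer that the FMD reading is unmasked, that the operator knows the visit, or that frames are picked by hand; the protocol states none of these. It equally does not say that the reading is automatic or how recordings are accepted, so the safeguard cannot be assumed either.

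A reader might also take a fixed figure such as 0.04 mm as the shift that equals the planned effect. The protocol gives no arterial diameter, so this is a conversion under an assumption. It holds only for an error in one diameter at one visit, and it says nothing about how likely such an error is.

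Nor does the protocol show that every baseline reading precedes every post-camp reading. It fixes the order within a subject only, and does not say whether there is one camp intake or several, or when recordings are read.

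Finally, the missing control group is the deeper limitation and masked reading does not cure it. That is correct. Masking removes one source of bias and leaves changes over time and acquisition differences in place.

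**Conclusion.** The point holds as an unguarded risk to the primary outcome; it is not a demonstrated bias. The protocol specifies masked counting for EPC migration and adhesion and specifies none for FMD, in a design where a visit-related reading shift passes directly into the estimate. At the planned 16 evaluable subjects, a shift of a quarter of the planned effect roughly doubles the false-positive rate to 11%, half the planned effect raises it to 30%, and a shift as large as the planned effect gives 82%. These figures assume no true change, a constant shift, and 1.3 as the SD of the change.

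The contrast should not be stretched to all EPC measures, because flow-cytometric EPC number has no masking statement either. The change is worth making before measurements start. It does not by itself invalidate the study.

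**What to change.** Add to the Endothelial function section, for example: *FMD recordings are stored, coded for subject and visit, and read in random order by an existing reader who is masked to visit. This reading is the primary outcome.* This presumes that the device's recordings can be stored and re-read, which the sponsor should confirm. If diameters are derived automatically, state that instead, and have recordings accepted or rejected by someone masked to visit.

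Masked reading does not address how the image was acquired. Therefore also state that the scan site within the 2 to 10 cm band is recorded at baseline and reused for the same subject after the programme.

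The cost is file coding, a short site record, and FMD results that arrive later. No visits are added, and the sample size stays at 16 evaluable and 20 enrolled. The lack of a control group remains a limitation to state when results are interpreted.

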**Heart rate variability**

HRV is used to determine the autonomic activity. The subjects will rest in the supine position for at least 10 min before the data are collected using the SphygmoCor device (AtCor Medical, Sydney, Australia). As for the time domain analysis, we will determine the standard deviation (SD) of normal-to-normal (NN) intervals (SDNN) and square root of the mean squared differences of successive NN intervals (RMSSD). SDNN is a measure of overall HRV, so a lower SDNN level indicates reduced overall HRV. RMSSD is a measure of parasympathetic autonomic function, and a reduced RMSSD is a marker of parasympathetic loss. For frequency domain analysis, total power (TP) in the frequency (0-0.40 Hz) will be divided into low-frequency power (LF: 0.04-0.15 Hz, modulated mainly by sympathetic system) and high-frequency power (HF: 0.15-0.40 Hz, modulated by parasympathetic system). Normalized units (nu) will be calculated by dividing the power of LF or HF by (LF+HF). LF/HF ratio reflects the complex interplay between sympathetic and parasympathetic modulation (sympathovagal balance). Increased sympathovagal balance is considered to reflect predominant sympathetic activity.

**Pulse wave velocity**

cfPWV will be measured using the SphygmoCor device (AtCor Medical, Sydney, Australia). The distance from the suprasternal notch to the carotid artery site (d-carotid) and the distance from the suprasternal notch to the femoral artery site (d-femoral) will be measured in meters using a standard measuring tape. A pressure sensitive transducer (tonometer) will be used on the carotid and femoral arterial sites along with three electrocardiogram leads attached to the participants' chest in order to measure the transit time of the pulse wave from the left ventricle to the carotid arterial site (t1) and from the left ventricle to the femoral arterial site (t2), respectively. The cfPWV will be calculated as the difference in distance between d-femoral and d-carotid divided by the mean difference between t1 and t2 (12). baPWV and cfPWV will be also measured with an oscillometric device (boso ABI-system 100; BOSCH & SOHN, Germany).

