**Pulse wave analysis**

Aortic pressure waveforms will be derived using a generalized validated transfer function (SphygmoCor, AtCor Medical, Sydney, Australia). The aortic pressure wave is composed of a forward wave, caused by stroke volume ejection, and a reflected wave that returns to the aorta from systemic sites. Augmentation pressure is the difference between the second and first systolic peaks. The augmentation index (AIx) will be defined as the augmentation pressure expressed as a percentage of the aortic pulse pressure.

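### Aerobic fitness is defined only per kg of body mass and cfPWV uses a taped surface distance, so weight loss alone raises the first and may lower the second

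*Protocol*

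**What the plan says.** **Aerobic fitness.** The Protocol, section *Aerobic fitness*, describes a cycle-ergometer test with the load set in watts and gives one definition of the result: "PWC150 or PWC170 is calculated as the power relative to body mass (W/kg) corresponding to the heart rate of 150 bpm or 170 bpm". Absolute watts are not named as an outcome. Section *Primary and secondary outcomes* lists aerobic fitness as secondary: "Secondary outcomes include anthropometry, resting heart rate, blood pressure, body composition, aerobic fitness".

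**cfPWV.** Section *Pulse wave velocity* states that the distances from the suprasternal notch to the carotid and femoral sites "will be measured in meters using a standard measuring tape". It then gives the formula: "The cfPWV will be calculated as the difference in distance between d-femoral and d-carotid divided by the mean difference between t1 and t2". It does not say how the tape is laid over the abdomen, or whether the distance is taken again at the second visit. It adds that "baPWV and cfPWV will be also measured with an oscillometric device", without giving that device's path-length method.

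**Programme and analysis.** Participants have a BMI of 30 or more and attend an 8-week weight-loss camp. Section *Diet intervention*: "Subjects will be provided with energy-restricted diets of 1300-2200 kcal/day based on weight". Section *Exercise training* plans an expenditure of 1500 to 2500 kcal/day through exercise, on a 6-days-a-week programme. There is one group, measured before and after, and section *Data analysis* compares the two visits by paired t-test at P < 0.05.

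**The concern.** Body mass is the denominator of the fitness index, and lowering body mass is what the programme is for. The index therefore rises with weight loss whether or not the subject can produce more power at the target heart rate. As the only fitness outcome, W/kg cannot separate a training effect from a weight effect.

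Taped distance is the numerator of cfPWV. A tape that follows the abdominal surface can read shorter after abdominal fat is lost. cfPWV would then fall, which reads as less stiff arteries, even though the pulse took the same time to travel.

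Both shifts point towards apparent benefit. With a single group there is no control arm in which the same shift would occur and cancel. At stake is how two secondary results are interpreted, not the primary FMD result.

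**Working it through.** **The plan's own figure.** The Protocol gives no expected size for W/kg or cfPWV. Its one planning figure is 20 subjects for FMD (change 1%, SD 1.3%, two-sided 5%, power 80%, 20% refusal). Reading 1.3% as the SD of the change, a paired t-test needs 16 (power 0.820), and 16 / (1 − 0.20) = 20. The figure reproduces, and this point does not touch it.

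**W/kg at unchanged watts.** Let P be the watts at the target heart rate, M the baseline mass and w the proportional weight loss. The index goes from P/M to P/[M(1 − w)], so the relative change is 1/(1 − w) − 1. The Protocol states no expected weight loss, so w is an assumed range.

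| Weight loss | Calculation | Rise in W/kg |
|---|---|---|
| 5% | 1/0.95 − 1 | 5.3% |
| 10% | 1/0.90 − 1 | 11.1% |
| 15% | 1/0.85 − 1 | 17.6% |

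The index can rise even when power falls: with 10% weight loss and watts down 5%, it changes by 0.95/0.90 − 1 = +5.6%.

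**Would the paired test pick this up?** The planned effect is 1/1.3 = 0.77 SD, which 16 evaluable subjects detect with probability 0.82. An 11.1% shift is 0.77 SD when the SD of the change is 11.1 × 1.3 = 14.4%. If that SD is 14.4% or smaller, weight loss of 10% alone gives P < 0.05 with probability of at least about 0.82. The Protocol gives no SD for W/kg, so this is a threshold, not a prediction.

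**cfPWV at unchanged transit time.** With path length D and transit time t, cfPWV = D/t. If the femoral distance reads c shorter and the carotid distance is unchanged, the relative change is −c/D, whatever t is. The Protocol gives neither D nor t. Assume D = 0.55 m and t = 0.07 s:

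- Baseline: 0.55/0.07 = 7.86 m/s.
- 2 cm shorter: 0.53/0.07 = 7.57 m/s, or −3.6%.
- 3 cm shorter: 0.52/0.07 = 7.43 m/s, or −5.5%.

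Over a wider assumed range (D from 0.45 to 0.55 m, c from 1 to 3 cm) the fall runs from 0.01/0.55 = 1.8% to 0.03/0.45 = 6.7%.

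**The case against.** **W/kg is a legitimate measure, openly defined.** This is fair. Power relative to mass is an accepted way to express fitness, and because weight is also measured, watts can be recovered from every W/kg value. No information is lost. A reader might go on to say that W/kg should be replaced, but that would be a preference. What stands is that the Protocol names no result in watts, so a significant gain in the one named result cannot be read as improved capacity.

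**The tape may be held straight, or the baseline distance reused.** The text allows either, and then nothing shifts. A reader might infer that cfPWV will fall as an artefact; the documents support only that it can. The text equally allows re-taping over the abdomen, and no rule prevents it.

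**The oscillometric device is a cross-check.** Only in part. It gives a second cfPWV and a brachial-ankle value, but its path-length method is not stated, so it cannot be assumed free of the same problem.

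**Augmentation index.** A reader might extend the point to this outcome, since it has no heart-rate standardisation and resting heart rate is itself an outcome. The documents do not support that. Section *Pulse wave analysis* says: "The augmentation index (AIx) will be defined as the augmentation pressure expressed as a percentage of the aortic pulse pressure". Heart rate is not a term in that formula, and the documents give neither a size nor a direction for any dependence on it.

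**Conclusion.** For aerobic fitness the point holds as arithmetic. Once weight falls, W/kg rises at unchanged watts, by 5.3% to 17.6% for losses of 5% to 15%. The only assumption is the amount of weight lost.

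For tonometric cfPWV it holds as a directional risk: about −3.6% to −5.5% for a path 2 to 3 cm shorter on an assumed 0.55 m. This depends on the distance being re-taped, on the tape following the abdomen, and on the arterial path itself not changing in 8 weeks.

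Both are secondary outcomes. The change is worth making, but nothing here bears on FMD or on the 20 subjects.

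**What to change.** **Section *Aerobic fitness*:** add absolute watts at the target heart rate as an analysed result beside W/kg, and state that any claim of improved fitness rests on the watts.

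**Section *Pulse wave velocity*:** state that each subject's baseline path length (femoral minus carotid distance) is used to compute tonometric cfPWV at both visits, so that a change in cfPWV can come only from transit time.

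**Cost:** two sentences. Watts are already needed to compute W/kg, and the baseline distances are already taken. No extra measurement, visit or subject is required.
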